- 2-minute walk with metronome beats and melody at 110% base cadence
- Break – 1 minute
- MDS-UPDRS III (section 3.9-13) – 2 minutes
- 2 minute-walk – 2 minutes

d. Blinding, including justification for blinding or not blinding the trial, if applicable.

Participants are blinded to the stimulation state (OFF or ON). Given the significant bias introduced by the patient knowing his/her/their stimulation status during the testing and generally wanting to perform “better” when their DBS system is activated, blinding/masking is required to capture the unbiased effect of RAS and/or stimulation.

e. Justification of why participants will not receive routine care or will have current therapy stopped.

The participants will have their DBS neurostimulators turned OFF and during washout period for approximately 35 minutes (washout period and testing period in DBS OFF state). Participants with DBS not infrequently experience their stimulators being turned OFF during routine clinical programming visits, and in the worst-case scenario, would NOT revert to having more prominent symptoms of Parkinson’s disease that they would experience had they never undergone this elective procedure. Participants with DBS routinely turn their DBS systems off for surgical procedures, MRI’s, and during clinical reprogramming sessions. The study requires this exposure in order to better understand the behavioral and neurophysiological mechanisms of RAS and DBS in improving patients’ gait patterns. Participants will be closely observed by study investigators and DBS specialist throughout the visit and can be reactivated immediately if any uncomfortable symptoms reemerge.

In some cases, the participants will require a DBS ON stimulation group that differs from their clinically optimized stimulation. In order to enable the recording capabilities of the Medtronic device, the sensing leads must be set above and below the stimulating leads. If the participants’ clinically optimized stimulation involves the middle leads, these exact same stimulation(s) can be used in the sensing mode. If not, the participant will receive a calibrated stimulation that mimics the clinically optimized stimulation as closely as possible. The participants will be monitored closely by both their clinician and the study clinician to ensure this difference is tolerated.

f. Justification for inclusion of a placebo or non-treatment group.

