Participants will be compared using their with and without RAS in DBS on/off state (within-subject comparison), thus, a placebo or non-treatment group will not be necessary.

g. Definition of treatment failure or participant removal criteria.

Participants will be removed from the study immediately if they experience any untoward symptoms during or after DBS being turned off (in this case DBS will be turned back on at the previously optimized settings).

- h. Description of what happens to participants receiving therapy when study ends or if a participant's participation in the study ends prematurely.

All participants will be instructed to continue their usual medications/stimulation once the study ends.

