A False Discovery Rate (FDR) correction will be used to account for multiple comparisons (Benjamini & Hochberg, 1995).

d. Early stopping rules.

Participants will be allowed to discontinue the testing at any time, and will be informed of this right during the consent. If a patient chooses to stop at any time during the testing, data already collected will be included in this research unless he/she specified that data should be withdrawn. Given the observational nature of the study, there is no interim analysis and are no early stopping rules.

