## 8. Risks

a. Medical risks, listing all procedures, their major and minor risks and expected frequency.

1. Loss of benefit of DBS when settings are changed during the experiment. This may allow Parkinson's (or dystonia) related stiffness, slowness of movement, or tremor to emerge. Stiffness can sometimes manifest as muscular discomfort, but this varies by patient. Essentially, the patients may return to their pre-DBS state just during the experimental period if all benefit of DBS is lost with the change in stimulation parameters. This is similar to when DBS is turned OFF for impedance checks or reprogramming during routine clinical visits.

2. Risk of falls: There will be a minimal risk of falls.

3. Clinical data breach. Clinical data about the participants are essential for answering the research question at hand. Potentially sensitive information, such as clinical diagnoses, medication dosages, and co-morbid conditions will be collected. If a data breach were to occur, this information could be available to others in the public, but the data would already have been de-identified (as described below).

4. Discomfort from MDS-UPDRS-III motor testing. Patients can sometimes experience physical fatigue while undergoing continuous motor batteries. Some patients may experience their performance on certain tasks as deficits and may feel some psychological discomfort from this.

b. Steps taken to minimize the risks.

1. To minimize the risk of discomfort from a loss of DBS efficacy when turned off, we have set the duration of the testing paradigm for “DBS-OFF” condition as at most 35 minutes so that the subject experiences the loss of benefit of DBS for limited amount of time. If severe Parkinson’s disease symptoms emerge when DBS is turned off (i.e. he/she returns to the “pre-DBS state”) and are not tolerated, we will return the participants DBS settings to his/her clinically effective programming. Symptoms should then resolve on the order of seconds to 5 minutes.
  2. To minimize the risk of falls, a research team member will walk alongside the patients during the assessments and study protocol.

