  6. Data Safety Monitoring Plan: Monitoring will be done by the study team during the study procedure. Given that there this is not a treatment trial, there are no long-term, cumulative safety outcomes to monitor. Study team will monitor the clinical state of participants enrolled in the study, especially having DBS settings changed. Any significant discomfort that would occur from either of these conditions would be immediately reversible by changing DBS back to the clinically optimized settings. Of note, any side effects from stimulation would be similar to what the patient might experience during a typical clinical encounter for DBS programming to target PD symptoms. Changes to DBS parameters take effect within seconds to 5 minutes.
- c. Plan for reporting unanticipated problems or study deviations.

Any adverse events, unanticipated problems, and/or study deviations will be reported to the IRB promptly, but no more than 10 days after discovery.

- d. Legal risks such as the risks that would be associated with breach of confidentiality.

A breach of confidentiality is theoretically possible, but because this is a single-site study without transmission of data between campuses or sites, and because all data will be maintained in one secure physical and/or electronic location, breach of confidentiality is exceedingly unlikely.

- e. Financial risks to the participants.

None.

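### Three sections set different triggers and consequences for symptoms with DBS off; the removal rule, read literally, can drop participants for the effect under study and pull the ON-OFF estimate toward zero

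*Protocol*

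**What the plan says.** Several places in the protocol deal with symptoms that appear while DBS is off.

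- Section 4g (removal criteria): "Participants will be removed from the study immediately if they experience any untoward symptoms during or after DBS being turned off". Stimulation is then switched back on.
- Section 4e (justification for interrupting therapy): participants "can be reactivated immediately if any uncomfortable symptoms reemerge". Removal is not mentioned.
- Section 8b item 1 (minimizing risk): if severe symptoms emerge "and are not tolerated, we will return the participants DBS settings to his/her clinically effective programming". Removal is not mentioned.
- Section 8b item 6 (safety monitoring): "Any significant discomfort that would occur from either of these conditions would be immediately reversible by changing DBS back to the clinically optimized settings". Removal is not mentioned.

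Section 8a says that loss of DBS benefit may allow disease-"related stiffness, slowness of movement, or tremor to emerge". Section 7d says: "If a patient chooses to stop at any time during the testing, data already collected will be included in this research", unless the patient asks for withdrawal of the data.

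Section 7c plans paired tests of the Wilcoxon type, both between phases within each state and between ON and OFF at each phase. About 10 participants are available, and the pilot is to supply an effect size for a larger study. The order of the two states is randomised (section 4a).

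**The concern.** There are two problems, and the second follows from the first.

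The sections do not agree on what triggers action or on what the action is. One ends participation; the others restore stimulation and say nothing about participation. Study staff facing mild, tolerated stiffness in OFF would end participation under 4g and carry on under 8b item 1.

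The 4g trigger also overlaps the outcome. Gait and MDS-UPDRS-III items in OFF measure the loss of benefit that 8a describes. If people leave because that loss shows, the OFF values (and, when OFF comes first, all the ON values) are missing for a reason tied to the outcome. The participants left in the paired comparison are then those who tolerate OFF best. The ON-OFF difference is understated, and that figure is meant to size the next study.

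**Working it through.** **1. The texts side by side**

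| Section | Trigger | Consequence |
|---|---|---|
| 4g | any untoward symptom | removal from the study, DBS on |
| 4e | any uncomfortable symptom | reactivation possible |
| 8b item 1 | severe and not tolerated | settings restored |
| 8b item 6 | significant discomfort | described as reversible |

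The clear conflict is 4g against 4e and 8b item 1.

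**2. Which data are lost**

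A signed-rank test uses only complete pairs. If OFF comes first, removal in OFF means that no ON value is ever taken, so every ON-OFF pair is lost. If ON comes first, only the OFF phases after removal are missing, and earlier pairs (pre-RAS, for example) survive. The statement in 7d that collected data are kept covers voluntary stopping, is silent on removal under 4g, and cannot supply values never measured.

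**3. Size of the bias**

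There is no plan figure to reproduce: the 10 is a count of available patients, with no effect size, SD, power or removal rate. The inputs below, apart from n = 10, are assumptions.

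- ON-OFF benefit D in SD units, normal with mean d = 0.8 and SD 1.
- k = 2 of 10 lost, namely the two highest on a symptom score that has correlation ρ with D.
- All pairs of those two are lost.

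The two largest of ten standard normal values have expectations 1.539 and 1.001, which sum to 2.540. The mean of the eight retained is expected to be

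d − ρ × 2.540 / 8 = 0.8 − 0.3175 ρ.

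The power column is from 20,000 simulated trials per row (exact two-sided Wilcoxon, unadjusted 0.05). With all ten pairs, power is about 60%.

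| ρ | Expected estimate (SD) | Shortfall | Power, 8 pairs |
|---|---|---|---|
| 0 | 0.80 | none | about 43% |
| 0.3 | 0.8 − 0.095 = 0.70 | 12% | about 35% |
| 0.5 | 0.8 − 0.159 = 0.64 | 20% | about 33% |
| 1.0 | 0.8 − 0.318 = 0.48 | 40% | about 29% |

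The ρ = 1 row is the extreme case. More than half of even its power loss (60% to 43%, of the fall to 29%) comes from having eight pairs instead of ten.

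The SD of the retained differences shrinks too, so the standardised effect falls less: to about 0.68 at ρ = 0.5 (15% lower) and about 0.61 at ρ = 1 (24% lower).

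**4. Other removal rates**

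At ρ = 1, losing 1 of 10 leaves 0.63 and losing 3 leaves 0.34. In a variant where each participant is removed with probability 20% and ρ = 0.5, the estimate is about 0.62; if half of those removed still give a complete pair at that phase, it is about 0.72.

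**5. Floor on the p-value**

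The smallest two-sided exact signed-rank p with n pairs is 2/2ⁿ: 0.002 for 10, 0.016 for 7, 0.031 for 6 and 0.0625 for 5. Losing five pairs rules out p < 0.05 even before the FDR correction.

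**The case against.** The best defence is that 4g need not be read literally. Section 8a anticipates emerging signs, section 4e says the OFF exposure is needed, and up to 35 minutes of OFF testing are planned. If anticipated signs counted as untoward, hardly any OFF data could be collected, so untoward may mean beyond what is expected. Section 4e is permissive and sets no removal rule, and all the texts agree that DBS can be turned back on. The exclusions in section 5 already keep out people with known discomfort, or expected severe worsening, when OFF. Missing-data rules may also sit in an analysis plan that is not shown.

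Much of this stands. It makes removals less likely and the size of any bias unknown. It does not remove the conflict: 4g says any, defines nothing as expected, and attaches a consequence that the other texts lack. The exclusions concern a much higher level of symptoms than the 4g trigger, and they narrow the sample in the same direction.

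A reader might go further in three ways that the protocol does not support.

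- That the estimate will be 40% too small and power 29%. This needs removal to follow the outcome perfectly, exactly two losses and no surviving pairs. Discomfort or tremor need not track cadence, stride length or LFP power.
- That data from removed participants will be discarded. Section 7d does not say so; it leaves them uncovered.
- That 7d contradicts 4g by stating that "there is no interim analysis and are no early stopping rules". That sentence can be read at trial level, whereas 4g concerns individual participants.

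**Conclusion.** The point holds as a conflict between stated rules with a conditional bias. Sections 4e, 4g and 8b give different triggers and consequences for the same event and must be reconciled; which clinical rule is right is not a statistical question. If 4g is applied literally and the symptoms that trigger it go with worse OFF performance, the ON-OFF estimate is pulled toward no effect. That link is plausible for gait and MDS-UPDRS-III and less certain for LFP.

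Under the assumed 0.8 SD with 2 of 10 lost, the shortfall runs from none (no correlation) through 12% and 20% (0.3 and 0.5) to 40% in the extreme case. The protocol supplies no effect size, removal rate or correlation, so no single figure can be defended. For a pilot of about 10 that makes no power claim, this is something that should be fixed rather than a fatal flaw. It matters mainly because the effect size is to be carried forward.

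**What to change.** 1. Reconcile 4e, 4g and 8b into one text with one trigger and one consequence for each event. The investigators set the clinical threshold.
2. Separate stopping the testing from removal from the study.
3. Extend 7d so that all data collected before any stop or removal, whoever decides it, are analysed unless the participant withdraws them.
4. Report stops and removals by stimulation state, order and time point, with reasons.
5. For the ON-OFF comparisons of gait and MDS-UPDRS-III only, add a sensitivity analysis in which an OFF assessment not done because of symptoms takes the worst rank.

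Worst rank should not be used in the pre-, during- and post-RAS comparisons within OFF. Someone stopped midway because DBS is off would be scored as doing worst under RAS, which charges the effect of DBS withdrawal to RAS. Nor should it be the main rule, since stopping for a symptom does not always mean the worst gait.

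The cost is wording in 4e, 4g, 7c, 7d and 8b, and one additional sensitivity analysis, which gives a rank-based result rather than a mean difference.

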## 5. Inclusion/Exclusion Criteria

### Inclusion criteria:

All participants will be adults (males or females) age 18 to 95 years old. In addition:

- diagnosed with idiopathic Parkinson's disease and have that diagnosis confirmed in the Johns Hopkins Parkinson's Disease and Movement Disorders Center
- underwent DBS Surgery (implanted Medtronic Percept™ PC DBS device in STN or GPi)
- fluency in English.

### Exclusion criteria:

- Participants who have dementia, language impairment, or severe motor impairment to the point that they cannot comprehend or understand instructions prior to recording.
- Participants who have known, significant discomfort when DBS is turned "off", even briefly.
- Participants who, in the view of the investigators, would have severely increased parkinsonian symptoms in the DBS OFF state potentially causing intolerable discomfort or disability

## 6. Drugs/ Substances/ Devices

- a. The rationale for choosing the drug and dose or for choosing the device to be used.

No drug or device is being studied. While the study includes patients under normal treatment with medications and brain stimulation. The participating patients already have DBS electrodes implanted for treatment of their movement disorder. We will only turn DBS off / on during the testing session, which is often done as part of clinical care during DBS reprogramming visits.

In particular, we will recruit participants implanted with the Medtronic Percept™ PC DBS device. This device is the first commercially available platform for patients with movement disorders that is capable of in vivo brain sensing. This allows us to deliver electrical stimulation and record the local field potential simultaneously.

In order to enable the recording capabilities of the Medtronic device, the sensing leads must be set above and below the stimulating leads. This requires a creation of a BrainSense Group, typically during the clinic visit prior to testing. For the DBS on condition, whenever compatible, the frequency, intensity, and electrode contact of stimulation will not be changed. If the exact same stimulation is not possible due to limitations of the Medtronic device mentioned above, the participant will receive a calibrated stimulation that mimics the clinically optimized stimulation as closely as possible. The

participants will be monitored closely by both their clinician and the study clinician to ensure this difference is tolerated.

b. Justification and safety information if FDA approved drugs will be administered for non-FDA approved indications or if doses or routes of administration or participant populations are changed.

N/A

c. Justification and safety information if non-FDA approved drugs without an IND will be administered.

N/A

## 7. Study Statistics

a. Primary outcome variable.

- Change in gait parameters (cadence, velocity, and stride length) before, during, and after RAS in each DBS ON and OFF state.
- Change in MDS-UPDRS-III (section 3.9-13) scores before, during, and after RAS in each DBS ON and OFF state.
- Change in power spectrum density of Local Fields Potential (LFP) (micro-volts-squared per Hz) before, during, and after RAS in each DBS ON and OFF state.
- Comparison of goals A, B, and C with and without melody.

b. Secondary outcome variables.

N/A

c. Statistical plan including sample size justification and interim data analysis.

- Sample size:

We will attempt to recruit all the patients in the movement disorders clinic who meet the inclusion criteria above. Per our clinic database, we have about 10 potential participants at this time. This pilot data will provide an effect size for a larger study.

- Data analysis:

All outcome measurements are continuous variable (time or scores).

- Independent variables: Stimulation state (ON, OFF), time point (pre-RAS, pure RAS, melodic RAS and post-RAS)
- Dependent variable 1: MDS-UPDRS-III (section 3.9: Arising from chair)
- Dependent variable 2: MDS-UPDRS-III (section 3.10: Gait)
- Dependent variable 3: MDS-UPDRS-III (section 3.11: Freezing of gait)
- Dependent variable 4: MDS-UPDRS-III (section 3.12: Postural stability)
- Dependent variable 5: MDS-UPDRS-III (section 3.13: Posture).
- Dependent variable 6: Cadence (steps/minute)
- Dependent variable 7: Velocity (meter/minute)
- Dependent variable 8: Stride length (meter)

- Dependent variable 9: Power spectrum density of Local Fields Potential (LFP) (micro-volts-squared per Hz)

The Shapiro-wilks test will be used to check the normality of the data.

We will use non-parametric paired-sample tests (e.g., Wilcoxon paired-sample test) as appropriate to compare the mean differences between pre-RAS, pure RAS, melodic RAS and post-RAS in each stimulation state (e.g., DBS ON-pre-RAS vs DBS ON-pure RAS vs DBS ON-melodic RAS, DBS ON-pre-RAS vs DBS ON-post-RAS, and DBS ON-pure RAS vs DBS ON-melodic RAS vs DBS ON-post-RAS; same comparison for DBS OFF state).

Further, the mean differences between DBS ON and OFF over each time period will be compared (e.g., DBS ON-pre-RAS vs DBS OFF-pre-RAS; DBS ON-pure RAS vs DBS OFF- pure RAS; DBS ON-melodic RAS vs DBS OFF- melodic RAS, DBS ON-post-RAS vs DBS OFF-post-RAS).

A False Discovery Rate (FDR) correction will be used to account for multiple comparisons (Benjamini & Hochberg, 1995).

d. Early stopping rules.

Participants will be allowed to discontinue the testing at any time, and will be informed of this right during the consent. If a patient chooses to stop at any time during the testing, data already collected will be included in this research unless he/she specified that data should be withdrawn. Given the observational nature of the study, there is no interim analysis and are no early stopping rules.

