### 1. Abstract

Parkinson Disease (PD) is a progressive neurodegenerative disorder that impacts both motor function (including tremor, rigidity, bradykinesia, and gait difficulty/postural instability) and nonmotor function (e.g., cognitive and mood impairments) (Armstrong & Okun, 2020).

Deep brain stimulation (DBS) has been used to manage motor fluctuations or complications of dopamine replacement therapy in patients with PD (Pötter-Nerger & Volkmann, 2013; Quinn et al., 2015). The Medtronic Percept™ PC DBS device is the first commercially available platform for patients with movement disorders that is capable of in vivo brain oscillation recording. This allows for simultaneous delivery of electrical stimulation and recording of the local field potentials.

Rhythmic auditory stimulus (RAS) is a Neurologic Music Therapy (NMT) technique that utilizes an auditory rhythmic cue to entrain gait to a specific rhythm. RAS, as an anticipatory time cue, can be used as both an immediate entrainment stimulus, providing rhythmic cues during movement, and as a facilitating stimulus for planning and executing movements to achieve more functional gait patterns. (M. Thaut & Hoemberg, 2014). The mechanism by which RAS exerts its effects in PD is unclear. It has been suggested that RAS can bypass the impaired frontostriatal gait networks in PD by recruiting cerebellothalamocortical networks; alternatively (or concurrently), RAS may augment the function of those frontostriatal networks (Koshimori & Thaut, 2018) .

Given the separate lines of evidence that RAS and DBS can help improve gait patterns, we propose this study to understand the behavioral and neurophysiological mechanisms of RAS and explore the clinical effects of RAS on DBS in patients with PD. To further explore the potential of music and deepen the understanding of RAS, this study will also be supplemented by a phase involving RAS with melody. The goal is to potentially develop a new tool to reinforce the effect of RAS.

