The protocol will consist of two parts (DBS OFF and DBS ON). The order of stimulation states will be randomly assigned to the participants. During DBS ON, participants will receive either their previously optimized stimulation or a calibrated stimulation that mimics their clinically optimized stimulation as closely as possible if the exact stimulation is not possible due to limitations of the Medtronic Device after a 10-minute wash-in/washout period. The researchers will measure participants' gait parameters (cadence, velocity, and stride length) with a 2-minute walk (a set distance of 10 meters during the 2-minute walk) and gait patterns using relevant items from the MDS-UPDRS-III rating scale during stimulation ON (Pre-RAS). The pre-RAS phase will be followed by an RAS intervention phase. The participants will then walk to the metronome beats for eight minutes (4 minutes for the same beat as baseline cadence and 4 minutes for 10% faster than baseline cadence) (RAS), and their gait parameters will be recorded. Within each set tempo, the participants will walk for 2 minutes to a pure metronome beat followed by a 2-minute walk with melody set to the same tempo. To counterbalance the effect of having the melody walk first, the order in which the participants first walk with

melody or without melody will also be randomly assigned. Between each of the 2-minute walks will be a 1-minute break. Finally, immediately after this walking bout, the same assessment as for Pre-RAS will be conducted (Post-RAS). Electrophysiological activity (local field potentials, LFPs) will be collected across all stages (pre, during, and post-RAS) of evaluation.

In DBS OFF, there will be a separate 10-minute washout period if it is taking place after DBS ONs so that the participant's brain circuits can adjust to not being stimulated. Except for the DBS stimulation state, DBS OFF will follow the same protocol as DBS ON above.

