### Primary goal:

- A. Comparison of gait parameters (cadence, velocity, and stride length) before, during, and after RAS in DBS ON and DBS OFF state.
- B. Comparison of MDS-UPDRS-III (items 3.9-13) scores in before, during, and after RAS in each DBS ON and OFF state.
- C. Comparison of power spectrum density of Local Fields Potential (LFP) (micro-volts-squared per Hz) in before, during, and after RAS in each DBS ON and OFF state.
- D. Comparison of goals A, B, and C with and without melody.

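### The listed comparisons test RAS within each DBS state and ON against OFF levels, but none estimates whether the RAS change differs between ON and OFF

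*Protocol*

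**What the plan says.** Protocol section 7.c names two crossed factors: "Independent variables: Stimulation state (ON, OFF), time point (pre-RAS, pure RAS, melodic RAS and post-RAS". The first primary outcome in section 7.a is "Change in gait parameters (cadence, velocity, and stride length) before, during, and after RAS in each DBS ON and OFF state"; the MDS-UPDRS-III and LFP outcomes are worded in the same way. Primary goal A in section 2 is the "Comparison of gait parameters (cadence, velocity, and stride length) before, during, and after RAS in DBS ON and DBS OFF state".

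Section 7.c then describes two families of paired non-parametric tests, with the Wilcoxon test as the example:

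1. Time points against one another within ON, and the same comparisons within OFF.
2. ON against OFF: "Further, the mean differences between DBS ON and OFF over each time period will be compared". The examples begin "DBS ON-pre-RAS vs DBS OFF-pre-RAS; DBS ON-pure RAS vs DBS OFF- pure RAS" and continue in the same way for melodic RAS and post-RAS.

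Each participant is tested in both states: "The order of stimulation states will be randomly assigned to the participants". The Abstract gives as one purpose to "explore the clinical effects of RAS on DBS in patients with PD". Section 7.c puts the available sample at about 10 and says that the pilot is to supply an effect size for a larger study.

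**The concern.** A question about RAS and DBS together is a question about a difference of changes: does gait or LFP power move more with RAS when stimulation is ON than when it is OFF? Neither listed family measures that. The first gives one verdict per state, and two separate verdicts are not a comparison of the two effects. The second compares levels, so any ON-OFF gap already present before RAS reappears during and after it.

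Two things are at stake. A reader of the results may take significance in one state but not the other as evidence that RAS depends on DBS. And the larger study would receive no effect size for the RAS-by-DBS question, because no listed comparison produces one.

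**Working it through.** The protocol states no effect size, SD, significance level or power, so it has no figure of its own to reproduce.

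**Which contrasts are covered.** Write the cell means as ON-pre, ON-RAS, OFF-pre and OFF-RAS.
- Family 1 estimates (ON-RAS − ON-pre) and, separately, (OFF-RAS − OFF-pre).
- Family 2 estimates (ON-pre − OFF-pre) and, separately, (ON-RAS − OFF-RAS).
- The contrast that addresses RAS by DBS is (ON-RAS − ON-pre) − (OFF-RAS − OFF-pre). It is in neither list and nowhere else in the protocol.

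**Inputs for the illustration.** From the protocol: n = 10 (about 10) and the Wilcoxon paired test. Assumed: normal data, SD of each within-state change = 1, two-sided 0.05 (actual size of the exact test 0.0488), no FDR step. The correlation between a participant's ON change and OFF change is unknown, so it is varied from 0 to 0.8.

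**Same true RAS effect in both states: how often is exactly one state significant?** With independent changes the formula is 2p(1 − p), where p is the power in each state.
- Effect 0.8 SD: simulated p is about 0.60, so 2 × 0.60 × 0.40 = 0.48. Direct simulation also gives 48%.
- Effect 0.5 SD: about 41%. Effect 1.0 SD: about 34%.

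The same people walk in both states, so independence is the extreme case. At 0.8 SD the figure falls from 48% at correlation 0 to about 35% at 0.5 and 23% at 0.8. The lowest value, about 17%, occurs at 1.0 SD and correlation 0.8. The range over the effect sizes tried is therefore roughly 17% to 48%. The formula's ceiling, at p = 0.5, is 2 × 0.5 × 0.5 = 50%. In these no-difference settings the direct test of the difference of changes rejects about 4.9% of the time, as it should.

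**Constant ON-OFF gap, same RAS effect (independent errors).** With a gap of 1 SD, the level tests reject about 79% of the time before RAS and about 79% during RAS. The two verdicts disagree in 33% of trials although nothing about RAS differs between the states. With a gap of 2 SD both reject almost always.

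**A true difference (1.6 SD ON, 0.8 SD OFF, gap 1 SD, independent errors).** RAS is significant in 99% of trials ON and 60% OFF, and the level tests reject in 79% (pre) and 99.8% (during). Both states being significant, and both level tests rejecting, are common outcomes here, and they are also common when the effects are equal. The listed tests do not separate the two situations.

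**Precision of the missing contrast.** With n = 10 and 80% power, the noncentral t gives a detectable difference of about 1.0 SD of the difference of changes (0.89 by the normal approximation). That SD equals √(2(1 − ρ)) times the SD of one within-state change: 1.41 at ρ = 0, 1.00 at ρ = 0.5, 0.63 at ρ = 0.8. In the 1.6 versus 0.8 SD case at ρ = 0, power is about 35%; at 2.4 versus 0.8 SD it is about 87%.

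**Cadence.** The cue is set at baseline cadence and at 10% above it. The protocol does not say outright that baseline is each part's own pre-RAS walk, but both parts follow the same procedure. On that reading, and if participants keep to the beat, cued-minus-pre cadence is about 0 at the first tempo and 0.10 × baseline at the second. Its ON-OFF difference is then 0 or 0.10 × (baseline ON − baseline OFF), which is set by the cue. Only post-minus-pre cadence is free of this.

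**The case against.** The strongest defence is that the tests fit the stated goals. Goals A to C and the primary outcomes ask about RAS in the ON and OFF states, for example "before, during, and after RAS in DBS ON and DBS OFF state", and none asks outright whether the effect differs by state. The interaction question rests on one exploratory phrase in the Abstract and on the crossing of the two factors. That stands, and it limits the severity.

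Both lists of comparisons are introduced as examples, and a statistical analysis plan could add the contrast. This stands in part. The list is not closed, but the protocol does set out the scheme, and every between-state example is a level comparison.

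The sentence on ON-OFF differences over each time period, read alone, could mean comparing those differences across periods, which would be the missing contrast. The examples that follow it rule this out.

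A reader might infer that the study cannot answer the RAS-DBS question at all. The documents do not support that: every participant is scheduled to supply all the cells, so the limit lies in the listed tests. A reader might also infer that the investigators plan to claim a differential effect from one significant and one non-significant result. The protocol nowhere says so; this is a risk in interpretation. The level comparisons validly show whether gait differs ON versus OFF under cueing, and the pre-RAS comparison listed beside them makes the baseline gap visible.

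Finally, a pilot of about 10 has little power for an interaction. That is true, and it is a reason to report an estimate rather than to leave the contrast out.

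**Conclusion.** The point holds as a should-fix. The listed comparisons give no estimate of whether the RAS change differs between ON and OFF, so the Abstract's exploratory aim is left without a matching analysis and the larger study without the corresponding effect size. The figure of 17% to 48% is illustrative: it depends on the assumed effect size and on an unknown correlation, and the FDR step would alter it. The structural conclusion, that neither family contains the contrast, depends on none of those assumptions. A higher grade is not warranted, because the primary goals do not explicitly pose the question, the study is a pilot without a confirmatory claim, and nothing in the design prevents the contrast from being computed.

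**What to change.** Add the following to section 7.c.

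- For velocity, stride length and LFP power, compute for each participant and state the cued-minus-pre-RAS change and the post-minus-pre-RAS change. Compare these changes between ON and OFF with the paired non-parametric test already planned. Report the estimate with its interval as the RAS-by-DBS effect for the larger study.
- For cadence, use post-minus-pre-RAS only.
- Keep the planned within-state and level comparisons, and state that a differential RAS effect will not be inferred from them.

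A mixed model with a state-by-time term is possible, but with only a random participant intercept it is not equivalent to the paired test: it relies on normality and a pooled residual error, which is a stronger assumption at this sample size.

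The cost is a few lines of analysis text, with no new data, procedures or participant burden. The price is precision: at about 10 participants only a difference of about 1.0 SD of the difference of changes is detectable with 80% power, so the result should be presented as an estimate and not as a confirmatory test.
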